
### Sample size calculation

According to the definition of the dominant population, at least one particular subgroup will have a positive outcome in terms of the primary efficacy index. A previous study conducted in Germany reported that approximately 13% of patients exhibited END on the third day after stroke onset (an increase of 2 or more points in the NIHSS score). Data obtained from our previous research as well as other domestic research showed that the rate of END on the third day after stroke onset was approximately 6–8%. The sample size was calculated on the following assumptions: the END rate in patients who did not receive the TCM intervention was 13% based on data from studies conducted overseas, and the END rate in patients who received the TCM intervention was 7% based on domestic data. Since there is no formula meant specifically for calculating the sample size in registry studies, we decided to use the one-sided difference test based on the statistical analysis method and formula for calculating the sample size in cohort studies. Consequently, the following formula, where α = 0.05 and β = 0.2, was used:
$$\text{n}={\left[\frac{Z_{1}-\alpha \sqrt{2\text{pq}}+Z_{1}-\beta \sqrt{{\text{p}}_{1}\left(1-{\text{p}}_{1}\right)+{\text{p}}_{2}\left(1-{\text{p}}_{2}\right)}}{{\text{p}}_{1}{-\text{p}}_{2}}\right]}^{2}.$$

The smallest sample size for a single cohort was estimated to be 426 patients; therefore, a minimum of 852 patients must be included. Considering the uneven distribution of exposure factors among patients and the inability of some patients to attend all the visits through the 90 days, the sample size was increased to 1,000 cases, which is an increase of 17% on the original base size.

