### Data processing and analysis

The mean (Mean), standard mean difference (SD), median (Median), interquartile ranges, minimum (Min), and maximum (Max) will be used to summarize continuous data, while rate or percentage will be used for categorical data. Between-group comparisons will be conducted using parametric or non-parametric tests, as appropriate. Pearson’s chi-squared test is used for the count data, and the results are expressed as rate or percentage (%). Measured data, if data are normally distributed and the variance is homogeneous, the parametric test (*t*-test) will be used and results will be expressed as mean ± SD; If the data are not normally distributed and still do not meet the requirements for the parametric test after data conversion, the non-parametric test (Wilcoxon rank sum test or Mann-Whitney U test) will be used and results will be expressed as median (Median).

As the primary analysis, a comparison of the presence of END on the third day after stroke onset will be conducted between the two groups of patients—the exposure group and the nonexposure group—using Pearson’s chi-squared test. The secondary outcome analyses will involve the rate of stroke-related and any-cause deaths, differences in the NIHISS scores, differences in the ICH scale scores, proportion of patients with BI scores ≥90, and proportion of patients with mRS scores ≤2. These analyses will be performed according to the standard statistical principles for comparing parametric or non-parametric distributions, as appropriate. During the analysis, multivariate linear regression analysis is performed for the influencing factors that are statistically significant in the univariate analysis. The full analysis set will be used in the efficacy correlation analysis in this study. The safety analysis set will be used in the safety analysis. The full analysis set refers to the set of eligible cases and detached cases but not eliminated cases. The safety analysis set will consist of safety indicators for all enrolled subjects with post-medication safety evaluation data; the number of subjects with missing data will be reported. All statistical tests will be one-sided, and statistical significance will be set at *p* < 0.05. SAS software, version 9.2 (SAS Institute, Inc., Cary, NC, United States), will be used to perform the statistical analyses.

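### The stated formula and inputs (one-sided alpha 0.05, beta 0.2) give 309 patients per cohort, not 426; the printed beta and the printed size cannot both be right

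*Protocol article*

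**What the plan says.** All inputs are in the protocol article, section Sample size calculation.

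- Rate without exposure: "the END rate in patients who did not receive the TCM intervention was 13% based on data from studies conducted overseas".
- Rate with exposure: "the END rate in patients who received the TCM intervention was 7% based on domestic data".
- Sidedness: "we decided to use the one-sided difference test". The section Data processing and analysis agrees: "All statistical tests will be one-sided, and statistical significance will be set at" p < 0.05.
- Error rates: "Consequently, the following formula, where α = 0.05 and β = 0.2, was used". The formula that follows is the usual pooled-variance one for two proportions with equal groups. It has no continuity term.
- Result: "The smallest sample size for a single cohort was estimated to be 426 patients; therefore, a minimum of 852 patients must be included".

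Only after this result does the article raise the total from 852 to 1,000, a 17% increase, to allow for uneven exposure and missed visits.

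**The concern.** Everything needed to repeat the calculation is printed, and the result does not follow from it. The number matters because 852 is presented as a floor for recruitment and the 17% margin up to 1,000 is measured from it. A reader is told that 852 patients give 80% power. If the printed size is the intended one, the design power is misreported. If the printed beta is the intended one, then the floor, the total and the percentage increase are all wrong.

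It also affects how the margin is judged. Exposure is observed, not allocated, so the groups may well be unequal. Whether 1,000 patients are enough at a given exposed share depends on whether the target was 80% or 90%.

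**Working it through.** **Inputs** (all from the article): p1 = 0.13, p2 = 0.07, difference 0.06, equal groups, so p = 0.10 and q = 0.90. One-sided alpha 0.05 gives z = 1.6449. Beta 0.2 gives z = 0.8416.

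**Formula as printed:** n = { [z(1−α)·√(2pq) + z(1−β)·√(p1(1−p1) + p2(1−p2))] / (p1 − p2) }².

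- √(2 × 0.10 × 0.90) = √0.18 = 0.42426
- √(0.13 × 0.87 + 0.07 × 0.93) = √(0.1131 + 0.0651) = √0.1782 = 0.42214

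**With the stated beta of 0.2:**

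n = [(1.6449 × 0.42426 + 0.8416 × 0.42214) / 0.06]² = [(0.69785 + 0.35528) / 0.06]² = 308.08, so 309 per cohort and 618 in total.

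The stated figure exceeds this by 426 − 309 = 117 per cohort, and 426/309 = 1.38.

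**Reproducing 426.** With beta 0.1 (z = 1.2816) and nothing else changed:

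n = [(0.69785 + 0.54099) / 0.06]² = 426.31. This is 426 if truncated and 427 (854 in total) if rounded up.

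**Other readings tried:**

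| Reading | n per cohort |
|---|---|
| One-sided, beta 0.2, as printed | 309 |
| One-sided, beta 0.2, unpooled variance | 307 |
| One-sided, beta 0.2, arcsine | 303 |
| One-sided, beta 0.2, continuity correction | 341 |
| One-sided, beta 0.15 | 359 |
| Two-sided, beta 0.2 | 392 |
| Two-sided, beta 0.2, continuity correction | 424 |
| **One-sided, beta 0.1** | **426.31 (427)** |
| Two-sided, beta 0.1 | 524 |

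**Power at 13% against 7%, equal groups, no continuity correction:**

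| Per cohort | One-sided 0.05 | Two-sided 0.05 |
|---|---|---|
| 309 | 80.1% | 70.1% |
| 426 | 90.0% | 83.2% |
| 500 | 93.6% | 88.7% |

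**The increase to 1,000.** 1,000/852 = 1.174, so 17% is right if 852 is right. From 618 it is 1,000/618 = 1.618, about 62%.

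**Unequal exposure at N = 1,000, one-sided, every patient evaluable on day 3.** Power is at least 80% for exposed shares of about 20% to 82%, and at least 90% only for about 31% to 70%. At a 25% exposed share it is 85.7%, which meets an 80% target but misses a 90% one. If 900 patients were evaluable (an assumption for illustration), the 80% range narrows to about 23% to 80%.

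**The case against.** Four points can be made on the other side.

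1. **The error is harmless in direction.** The stated minimum is larger than the stated inputs need. The recruitment target, the primary test and its alpha do not change. This is correct: it limits the consequence to a misreported calculation, but it does not make the calculation right.

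2. **The cause is inferred.** Beta 0.1 is the closest match, but the article does not say whether beta or n is the slip. A two-sided calculation at beta 0.2 with continuity correction gives 424, within 0.5% of 426. It therefore remains a possible origin of the number. It does not rescue the text, because it contradicts the stated one-sided test, the one-sided rule in the analysis section and the printed formula. It also still misses 426.

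3. **An allowance for dropout or uneven exposure could already be inside 426.** The article rules this out, since it adds that allowance afterwards, in going from 852 to 1,000.

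4. **The difference between 426 and 309 should not be called spare capacity.** If 90% power was intended, nothing is spare. This stands, so the verdict makes no claim on those patients.

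The conversion from PDF does not explain the mismatch either. The rates, alpha, beta and n are legible prose. The formula's subscripts are garbled, but its structure is the standard one and it yields the article's own figure at beta 0.1.

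**Conclusion.** The point holds. The printed formula with the printed inputs requires 309 patients per cohort (618 in total), and the article states 426 (852), which is 38% more. The stated beta of 0.2 and the stated size are mutually inconsistent. At 426 per cohort the power is 90.0%, not 80%.

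This rests on the article's own rates of 13% and 7%, equal groups, a one-sided 0.05 test and no continuity correction. All are stated or implied there. Beta 0.1 is the most likely explanation, but the document does not prove it. On these assumptions the study is not underpowered at balanced exposure. What is wrong is the stated basis for its size.

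**What to change.** Keep N = 1,000 and correct the paragraph in one of two ways, according to what was intended:

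- **If 90% power was intended:** state beta 0.1. Give 427 per cohort and 854 in total, or keep 426 and 852 and say the result was truncated. The 17% increase stands either way (1,000/854 = 1.171).
- **If 80% power was intended:** keep beta 0.2, state 309 per cohort and 618 in total, and restate the increase to 1,000 as about 62%.

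If 426 came from a different method, such as a two-sided calculation with continuity correction, the method, sidedness and formula should be rewritten to match the one used.

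It would help to add one sentence giving the power of 1,000 patients over a plausible range of exposed shares, with the assumed number evaluable on day 3, since uneven exposure is a stated reason for the increase.

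The cost is one corrected paragraph. Recruitment, data collection and the primary test do not change.

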### Qualitative research

Qualitative research will be conducted based on the results of the quantitative research. The emergency doctors participating in this study will be interviewed via one-to-one semi-structured interviews or group interviews, lasting approximately 60 min/person. The number of interviewers will be determined based on the results of three to five pre-interviews. According to the degree of information saturation, approximately 20 doctors will be interviewed. The interview will be mainly about the knowledge and attitude of the emergency doctors regarding XNJI used for stroke first aid. The process is as follows:• Interview sampling: Purposive sampling. Depending on the degree of information saturation, approximately 20 individuals will be interviewed based on the results of the pre-interviews.• Interview place: Beijing 120 Emergency Center.• Interview time: Approximately 60 min/person.• Data collection: A basic personal questionnaire will be used to collect data, such as the name, sex, age, education background, professional title, years of first aid work, professional physician certificate category, etc. During this research process, the content of the interviews of participating doctors will be documented in detail to help researchers in understanding the respondent’s basic information.

### Data processing and analysis

The mean (Mean), standard mean difference (SD), median (Median), interquartile ranges, minimum (Min), and maximum (Max) will be used to summarize continuous data, while rate or percentage will be used for categorical data. Between-group comparisons will be conducted using parametric or non-parametric tests, as appropriate. Pearson’s chi-squared test is used for the count data, and the results are expressed as rate or percentage (%). Measured data, if data are normally distributed and the variance is homogeneous, the parametric test (*t*-test) will be used and results will be expressed as mean ± SD; If the data are not normally distributed and still do not meet the requirements for the parametric test after data conversion, the non-parametric test (Wilcoxon rank sum test or Mann-Whitney U test) will be used and results will be expressed as median (Median).

As the primary analysis, a comparison of the presence of END on the third day after stroke onset will be conducted between the two groups of patients—the exposure group and the nonexposure group—using Pearson’s chi-squared test. The secondary outcome analyses will involve the rate of stroke-related and any-cause deaths, differences in the NIHISS scores, differences in the ICH scale scores, proportion of patients with BI scores ≥90, and proportion of patients with mRS scores ≤2. These analyses will be performed according to the standard statistical principles for comparing parametric or non-parametric distributions, as appropriate. During the analysis, multivariate linear regression analysis is performed for the influencing factors that are statistically significant in the univariate analysis. The full analysis set will be used in the efficacy correlation analysis in this study. The safety analysis set will be used in the safety analysis. The full analysis set refers to the set of eligible cases and detached cases but not eliminated cases. The safety analysis set will consist of safety indicators for all enrolled subjects with post-medication safety evaluation data; the number of subjects with missing data will be reported. All statistical tests will be one-sided, and statistical significance will be set at *p* < 0.05. SAS software, version 9.2 (SAS Institute, Inc., Cary, NC, United States), will be used to perform the statistical analyses.

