### Intervention measures

The quantitative research part of this study will be observational. Based on our observation of whether XNJI was intravenously administered within 24 h of onset in the prehospital ambulance setting, patients with acute stroke will be divided into two groups: the exposure group comprising patients who were intravenously administered XNJI and the nonexposure group comprising patients who were not. During the study period, all relevant data will be collected at the following timepoints to facilitate a continuous dynamic observation and evaluation: during the prehospital ambulance service; within 24 h of admission; day 3 after stroke onset; day 10 after stroke onset or the day of discharge; and 30 ± 3, 60 ± 3, and 90 ± 7 days after stroke onset. This research will not interfere with the actual diagnosis and treatment of the participants. The clinicians will make decisions regarding routine treatment options based on the patient’s specific circumstances. The routine stroke treatment will follow the current national guidelines for acute Is and ICH from the Chinese Society of Neurology.

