### Main variables

All variables used for outcomes evaluation of efficacy and safety are abstracted from all relevant data collected during the observation period. The main variables of this study are listed in Table 1.

**TABLE 1 T1:** Main variables registered in the TRACE study.

Field	Variables
Visit 1 (during pre-hospital ambulance service)	
Demographics information	Name; Age; Gender; ID number
Condition, state of consciousness, and survival or death upon ambulance arrival	Time of symptom onset; Time of ambulance arrival; State of consciousness; Survival/death; Stroke assessment (BEFAST)
Usage of XNJI	Use it or not; Time of first use of XNJI; Dose
Concomitant medication	Antihypertensive drugs; Vasopressor drugs; Hypoglycemic agent; Glycemic drugs; Other drugs
Auxiliary examination	Vital signs
Indicators on health economics	Treatment costs; Inspection fees; Medicine costs; Other costs; Total costs
Prehospital evaluation	NIHSS
Visit 2 (within 24 h after admission)	
Condition, state of consciousness, and survival or death upon arrival	Time of onset, Time of arriving at the hospital; State of consciousness; Survival/death
Baseline information	Height; Weight; BMI; Being overweight or obese; Predisposing factors; Transient symptoms occurred within 2 months before stroke onset; Past medical history (strokes; CHD; atrial fibrillation; diabetes; hypertension; hyperlipidemia; apnea); Personal history (smoking; alcohol consumption); Family history; Drug allergy history; Treatment history within 2 weeks before admission
Auxiliary examination	Vital signs; Laboratory tests; Cranial CT or MRI; ECG
Complication	Lung infections; Urinary tract infections; Upper gastrointestinal bleeding; Hiccups; Dysphagia; Urine retention; Urinary incontinence; Pressure ulcers; Kidney failure; Pulmonary embolism; Epilepsy; Shoulder-hand syndrome; Post-stroke depression; Post-stroke anxiety; Others
Admission evaluation	mRS; NIHSS; ICH Scale and GCS for ICH
Visit 3 (day 3 after symptom onset)	
Auxiliary examination	Vital signs
Complications	Lung infections; Urinary tract infections; Upper gastrointestinal bleeding; Hiccups; Dysphagia; Urine retention; Urinary incontinence; Pressure ulcers; Kidney failure; Pulmonary embolism; Epilepsy; Shoulder-hand syndrome; Post-stroke depression; Post-stroke anxiety; Others
In-hospital evaluation	NIHSS; ICH Scale and GCS for ICH
Visit 4 (day 10 after symptom onset or the day of discharge)	

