### Types of outcomes

#### Efficacy outcomes

The primary outcome is END on the third day of onset defined as an increase of 2 or more points in the NIHISS score between baseline and day 3. The secondary outcomes include the rates of stroke-related and any-cause deaths during hospitalization, differences in the changes in the neurological deficit degree, risk grade of ICH evaluated through changes in the ICH scale score from baseline to day 10 or the day of discharge, the proportion of patients with activities of daily living with a Barthel Index score of ≥90, and the proportion of independent patients defined by a modified Rankin Scale score ≤2 at 30 ± 3, 60 ± 3, and 90 ± 7 days after stroke onset. A complete list of the efficacy outcomes analyzed in the TRACE study is presented in Table 2.

**TABLE 2 T2:** | The complete list of efficacy outcomes analyzed in the TRACE study.

Primary outcome
1. Early neurological deterioration# change
Early neurologic deterioration (END) is defined as an increase of 2 points or more in the National Institute of Health Stroke Scale (NIHSS) score between baseline and 3 days. The NIHSS score ranges from 0 (best score) to 42 (worst score). [Time Frame: between baseline and 3 days]
Secondary outcomes
1. Rate of stroke-related deaths and deaths from any cause Rate of stroke-related deaths and deaths from any cause during hospitalization [Time Frame: during hospitalization] 2. Neurological deficit Comparison of the change of degree of neurological deficit evaluated by the NIHSS [Time Frame: baseline and day 10 or the day of discharge] 4. Risk grade of a cerebral hemorrhage Comparison of the change of risk grade of Intracranial hemorrhage evaluated by Intracerebral Haemorrhage (ICH) scale. The ICH score ranges from 0 (best score) to 6 (worst score). [Time Frame: baseline and day 10 or the day of discharge] 5. Activities of daily living Activities of daily living will be measured by Barthel Index (BI) score. The proportion of patients with a BI score of ≥ 90. The BI score ranges from 0 (worst score) to 100 (best score). [Time Frame: 30, 60, and 90 days] 6. The proportion of patients’ independent The proportion of patients’ independence is defined as a modified Rankin Scale (mRS) score of ≤ 2. The mRS score ranges from 0 (best score) to 6 (worst score). [Time Frame: 30, 60, and 90 days]

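### The primary analysis of a non-randomised exposure is an unadjusted chi-squared test, so confounding can bias the main END result in either direction

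*Protocol article*

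**What the plan says.** Under Intervention measures: "The quantitative research part of this study will be observational". The two groups are formed "Based on our observation of whether XNJI was intravenously administered within 24 h of onset in the prehospital ambulance setting". The same section adds: "The clinicians will make decisions regarding routine treatment options based on the patient’s specific circumstances".

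Under Efficacy outcomes, the primary outcome is binary: "END on the third day of onset defined as an increase of 2 or more points in the NIHISS score between baseline and day 3".

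Under Data processing and analysis: "As the primary analysis, a comparison of the presence of END on the third day after stroke onset will be conducted" between the exposure and nonexposure groups, "using Pearson’s chi-squared test". All tests are one-sided at 0.05. The only multivariable step in the article is one sentence placed after the secondary outcomes: "multivariate linear regression analysis is performed for the influencing factors that are statistically significant in the univariate analysis". No matching, weighting, propensity score or stratification (for example by ischaemic stroke or haemorrhage) is stated anywhere.

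The Abstract gives the main purpose as finding out whether prehospital XNJI protects patients from END. The limitations in the Discussion are short follow-up, the preset case form and restriction to Beijing. Confounding is not among them.

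**The concern.** When nobody randomises the exposure, exposed and nonexposed patients may differ in severity, consciousness, stroke type, age or time since onset. Each of these may also predict END. A crude comparison of END proportions mixes those differences with any effect of XNJI.

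The regression sentence does not repair this. A linear model is an odd choice for a binary outcome. A confounder that misses univariate significance would be left out, whatever its clinical importance. Nothing says that the model is applied to END or that its result takes precedence over the chi-squared test.

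At stake is the main conclusion. The article lists END as an efficacy outcome and sizes the study on a one-sided difference of 13% versus 7%, so the primary p-value invites a causal reading that the test cannot support.

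**Working it through.** **Inputs from the plan** (Sample size calculation; Data processing and analysis): one-sided alpha 0.05; N = 1,000; END 7% exposed and 13% nonexposed, midpoint 10%. The exposure share, the predictors of XNJI use and the strength of any confounder are not given. Everything about them below is an assumption.

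**1. The plan's own figures.** The printed formula with the stated errors gives [(1.645×√0.18 + 0.842×√0.1782)/0.06]² = 308.1 per cohort, not 426. With 90% power it gives 426.3. That mismatch is a separate matter and does not bear on this point. With 500 per group, power = Φ[(0.06 − 1.645×0.01897)/0.01888] = Φ(1.525) = 93.6%. This figure presupposes comparable groups.

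**2. No true effect, milder patients more often exposed.** Assume 500 per group, overall END 10%, and one binary prognostic factor with risk ratio R for END, present in a fraction f of a group (f averages 0.5 over the two groups).
- Risk without the factor: p0 = 0.10/[1 + (R−1)×0.5]
- Group risk: p0×[1 + (R−1)×f]
- Chance that the test declares benefit: Φ[(p_non − p_exp − 1.645×SE0)/SE1], with pooled SE0 and unpooled SE1

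Example, R = 2, f = 40% exposed and 60% nonexposed: p0 = 0.10/1.5 = 0.0667. END is 0.0667×1.4 = 9.3% and 0.0667×1.6 = 10.7%. Then Φ[(0.0133 − 0.0312)/0.01897] = Φ(−0.94) = 17%.

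| R | Factor, exposed vs nonexposed | END, exposed vs nonexposed | Chance of declaring benefit |
|---|---|---|---|
| any | 50% vs 50% | 10.0% vs 10.0% | 5% |
| 2 | 40% vs 60% | 9.3% vs 10.7% | 17% |
| 2 | 30% vs 70% | 8.7% vs 11.3% | 41% |
| 3 | 40% vs 60% | 9.0% vs 11.0% | 28% |
| 3 | 30% vs 70% | 8.0% vs 12.0% | 68% |
| 2 | 60% vs 40% | 10.7% vs 9.3% | under 1% |

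The increase to 1,000 patients, made partly for uneven exposure, does not help. At 426 per group the 17% and 68% become 16% and 62%. More patients reduce variance and leave the bias in place.

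**3. A true effect, sicker patients more often exposed.** Assume 40% severe patients with END 18%, the others 6%, and XNJI given to 70% of severe and 40% of milder patients.
- Exposed: 280 + 240 = 520, of whom 280/520 = 53.8% severe. Nonexposed: 120 + 360 = 480, of whom 25% severe.
- With no effect: 0.06 + 0.12×0.538 = 12.5% versus 0.06 + 0.12×0.25 = 9.0%, crude risk ratio 1.38.
- With a true risk ratio of 7/13 = 0.54: 6.7% versus 9.0%, crude risk ratio 0.75.
- Power: Φ[(0.0229 − 1.645×0.01698)/0.01706] = Φ(−0.295) = 38%. Without confounding, the same group sizes and overall risk give 89%.

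A weaker imbalance costs less. For 7% versus 13% with 500 per group, the factor in 60% of exposed and 40% of nonexposed lowers power from 94% to 80% (R = 2) or 69% (R = 3).

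**4. Room for adjustment.** At the planned rates, 500×0.07 + 500×0.13 = 100 END events. The 20 sites as fixed effects use 19 parameters, about 5 events each, before any clinical covariate enters.

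**The case against.** **An intent to adjust is stated, and a separate statistical plan may give the details.** The regression sentence is not labelled secondary, and Data collection and management does mention a statistical plan. But the article names the chi-squared test as primary. A statistical plan could make an adjusted analysis primary only by contradicting that published sentence.

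**The study claims only preliminary evidence of a relationship, and the Discussion calls for randomised trials.** This stands in part, and it is not certain that readers would take the crude p-value as the effect. Still, the stated purpose is protective and the limitations do not mention confounding.

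**The sentence on clinicians' decisions concerns routine treatment, not XNJI in the ambulance specifically.** True. That clinicians select patients for XNJI is a fair inference and not a stated fact. The groups are non-randomised either way.

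**Stronger readings that the documents do not support.** A reader might infer that confounding by indication determines the result, or that it must favour XNJI. With no exposure share, no predictors of use and no confounder strength given, neither can be shown. A reader might also infer that every confounder needed is already recorded before exposure. Table 1 does not list the receiving hospital, and nothing shows that it was settled before XNJI was given. The article does not say whether prehospital NIHSS precedes XNJI, and the note to Table 2 lets baseline NIHSS be taken after admission.

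**Conclusion.** The point holds. The plan fixes an unadjusted test as the primary analysis of a non-randomised exposure, and its one regression sentence does not repair that. The main END result can be biased in either direction; how far, and which way, cannot be known from the documents.

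The illustrated sizes are a false-benefit chance of about 17% to 68% against a nominal 5% when milder patients are more often exposed, and dilution of a true risk ratio of 0.54 to 0.75 with power about 38% when sicker patients are. They rest on assumed confounder strengths and imbalances and on a single binary factor, so they are examples and not predictions. Because the defect lies in the primary analysis and bears on the main conclusion, it should be corrected before the data are analysed.

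**What to change.** By a dated amendment before data lock and analysis, make a confounder-adjusted estimate for binary END the primary analysis. Use propensity-score weighting, or logistic or log-link regression with robust standard errors. Report the adjusted risk difference and risk ratio with confidence intervals, and keep the chi-squared test as descriptive.

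Prespecify a short covariate list on clinical grounds, limited to variables measured before XNJI or not affected by it:
- age and sex
- stroke type (ischaemic or haemorrhagic)
- onset-to-ambulance time
- state of consciousness on ambulance arrival
- key medical history
- prehospital NIHSS, where it is recorded before XNJI

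Do not treat a post-admission NIHSS as a pre-exposure covariate. With about 100 expected events, handle site by clustering, a random effect or the propensity model, not by 20 fixed effects.

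Cost: some loss of precision compared with the crude estimate, modest extra programming, and the amendment itself. Recruitment was due to end in December 2022, so the amendment must be dated before anyone examines END by exposure. The listed variables are in Table 1 or follow from the imaging and times recorded there, so no new patients are needed.
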